### Outcome measures

#### Primary outcome

The primary outcome measure is mobility on discharge from hospital as assessed using gait speed. This will be measured using the 6-meter walk test [27] at self-selected speed by a trained assessor blinded to group allocation. Participants will be instructed to walk at self-selected speed along a 10-meter walkway, and a stopwatch will be used to measure speed over the middle 6 meters. Participants will be allowed to use a gait-aid if required, and this will be recorded. Up to three trials will be performed, and the best performance recorded. Participants unable to complete the test will be given a score of 0 m/sec. Gait speed was chosen as a primary outcome measure as it is associated with the need for long-term care [8], functional dependence, mortality [9] and falls [10]. Gait speed can also predict activity levels at home and in the community [28,29] and increases in gait speed are associated with improvements in overall health status [30]. Furthermore, gait speed has good retest reliability [27,31] and is responsive to changes in walking ability [32-34].

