### Sample size estimation

The sample size for this study was calculated based on pilot data, which showed that the median gait speed of people discharged from aged care rehabilitation was 0.46 m/sec (range 0.1 to 1.2 m/sec) [6], which allowed a mean gait speed (0.46 m/sec) and variance (0.18 m/sec) to be estimated [50]. Sample size estimation was based on the intervention group achieving an increase in gait speed of at least 0.1 m/sec compared with the control group, the recommended minimal clinically important difference for gait speed in older adults [30,51]. With a two-tailed significance threshold alpha of 0.05 and power to yield a statistically significant result set at 90%, a sample size of 69 participants in each group is required. To account for an estimated 25% dropout rate and 14% of participants being unable to complete the walk test on discharge, as observed in pilot data [6,25], an estimated 198 participants will be required in total [52]. A recruitment rate of 34% was achieved in the pilot study. Based on average hospital admissions to the selected sites in this trial, and using a conservative recruitment rate of 20%, it is anticipated that the recruitment will be completed over 13 months.

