### Statistical analysis

The primary analysis will be conducted on an intention-to-treat basis using data from all randomized participants, although a ‘per protocol’ analysis of the primary outcome will also be reported. Primary outcome values missing due to participants’ death will be imputed as zero. An independent adjudication panel, blinded to group assignment, will review records for participants’ who were discharged to an acute facility as medically unwell. Based on the reasons for transfer, the adjudication panel will determine whether the participant was likely to be able to walk and complete a 6-meter walk test at the time of transfer. If the adjudication panel determines the person was unlikely to be able to walk, the missing value will be imputed as zero. If the adjudication panel determines the person was likely to be able to walk, the last measure will be carried forward. Following that, multiple imputation of other missing primary outcome values will be conducted subject to the satisfaction of relevant missingness assumptions. Baseline data will be examined to ensure that the intervention and control groups are comparable using descriptive statistics with 95% confidence intervals.

All outcomes and analyses have been prospectively categorized as primary, secondary, or tertiary. Differences in both primary and secondary endpoints between the two arms of the study will be tested independently at the 0.05 level of significance. No formal adjustments will be undertaken to constrain the overall type I error associated with the secondary analyses. Their purpose is to supplement evidence from the confirmatory primary analysis to help more fully characterize the treatment effect. Results from the secondary analyses will be interpreted in this context.

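### The stated 90% power was calculated for gait speed among people who can walk, but the primary analysis also includes non-walkers, scored 0 m/sec

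*Protocol article*

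**What the plan says.** In Sample size estimation, the planning figures come from an earlier cohort with speeds from 0.1 to 1.2 m/sec, "which allowed a mean gait speed (0.46 m/sec) and variance (0.18 m/sec) to be estimated". The target effect is the "intervention group achieving an increase in gait speed of at least 0.1 m/sec compared with the control group". With two-sided alpha 0.05 and 90% power this gives 69 per group. The total then rises to 198 for 25% dropout and for "14% of participants being unable to complete the walk test on discharge".

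The Primary outcome section treats the same people differently: "Participants unable to complete the test will be given a score of 0 m/sec".

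Statistical analysis includes all randomized participants and adds further zeros: "Primary outcome values missing due to participants’ death will be imputed as zero". Participants transferred to acute care whom a blinded panel judges unlikely to be able to walk are also set to zero. Those judged likely to walk have their last measure carried forward, and other missing values are multiply imputed.

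Primary outcome analysis specifies ANCOVA with baseline gait speed as covariate. The sample-size section mentions neither ANCOVA nor a correlation.

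**The concern.** The same 14% cannot be both lost data and analysed values of zero. If they are analysed, the outcome is a mixture: a block of zeros plus the walkers' speeds. Its variance has a component from the gap between zero and the walkers' mean, which the planning SD leaves out.

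The meaning of the 0.1 m/sec effect also becomes unclear. It could be a difference in means over everyone, zeros included, or a gain among walkers only, and these are different targets.

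The abstract says that the study is powered for 0.1 m/sec, and a null result would be read against that statement. At stake is the planning justification. The effect estimate and the type I error rate are not affected.

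**Working it through.** **Reproducing the plan's figures.** Per group, n = 2 × [SD × (1.960 + 1.282) / difference]². With SD 0.18 and difference 0.1 this is 68.1, rounded up to 69, as stated. The 0.18 is labelled a variance but was used as an SD; read as a variance it would give 379 per group.

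Then 69 × 1.25 × 1.14 = 98.3, rounded up to 99 per group, or 198 in total. Dropout alone gives fewer: 69 / 0.75 = 92 per group, or 184. So the 14% was applied as a loss.

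**Whose SD is 0.18?** The source range starts at 0.1 m/sec, so it contains no zeros. The Background reports, for the same cohort, the 14% who could not walk 10 meters as a separate figure. The SD therefore describes walkers.

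**SD of the score as analysed.** With a share p of zeros, variance = (1 − p) × SD² + p × (1 − p) × mean². For p = 0.14, walkers' mean 0.46 and SD 0.18:
- 0.86 × 0.18² = 0.0279
- 0.14 × 0.86 × 0.46² = 0.0255
- sum 0.0533, so SD = 0.231

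The planning variance is 0.18² = 0.0324, so the variance rises by about 65%.

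**Number analysed.** If the whole 25% dropout is lost, 198 × 0.75 / 2 = 74.25 per arm, about 74. If every participant contributes, it is 99 per arm. The upper figure is a bound, because deaths and adjudicated transfers do receive values but multiple imputation does not fully recover lost information. The article does not say how the 25% divides.

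**Unadjusted power** (two-sided 0.05, two-sample t-test):

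| Overall difference | SD | 74 per arm | 99 per arm |
|---|---|---|---|
| 0.1 | 0.231 | 75% | 86% |
| 0.86 × 0.1 = 0.086 | 0.231 | 62% | 74% |

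The second row assumes that only walkers gain and that the share of zeros is equal in both arms. It uses the control-arm SD for both arms. With walkers' mean 0.56 in the intervention arm, the averaged SD is 0.244 and power is about 57% to 69%.

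For a difference of 0.1, 90% unadjusted power needs 113 analysed per arm. If the share of zeros is assumed to be 10% or 20% instead of 14%, power for 0.1 is 79% or 70% at 74 per arm, and 89% or 82% at 99 per arm.

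**Effect of ANCOVA.** Residual SD = 0.231 × √(1 − r²), where r is the baseline-to-discharge correlation of the zero-inclusive score. For a difference of 0.1, 90% power needs r of about 0.59 at 74 per arm or 0.35 at 99 per arm. At assumed values, r = 0.5 gives 86% and r = 0.6 gives 91% at 74 per arm; r = 0.4 gives 91% at 99 per arm.

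**If treatment also reduces non-walking.** Suppose zeros fall from 14% to 10% in the intervention arm and walkers gain 0.1. The difference is 0.90 × 0.56 − 0.86 × 0.46 = 0.504 − 0.396 = 0.108, the averaged SD is 0.235, and unadjusted power is about 80% to 90%.

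**The case against.** The strongest reply is that none of the unadjusted figures is the power of the planned test. The primary analysis is ANCOVA, and a moderate correlation could restore 90%. Taking zero correlation is as much an assumption as taking 0.5. This stands, and it rules out a conclusion that a reader might draw, namely that the trial lacks its stated power. The document gives no correlation from which to decide this.

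Three further points have weight:
- **Keeping the 14% in the analysis adds participants.** Some of the 25% dropout may also receive values under the death and transfer rules. Counting such people both as losses and as extra zeros would charge them twice, so the range of 74 to 99 per arm has to be shown. Even at 99, unadjusted power for 0.1 is 86%.
- **Dilution to 0.086 is not stated in the plan.** The plan sets 0.1 m/sec as a between-group difference and does not confine it to walkers. Non-ambulant patients are enrolled and receive sit-to-stand, standing and stepping exercises as able, so the share of zeros could fall.
- **The Background's interquartile range of 0.32 suggests a larger SD among walkers.** That questions how 0.18 was derived, which is a separate matter, and no figure here relies on it.

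The point cannot be set aside as detail left to an analysis plan. The article gives a complete calculation and an explicit scoring rule, and the two conflict.

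**Conclusion.** The point holds as an inconsistency between the power calculation and the endpoint. The 90% was computed for walkers' gait speed, with non-walkers counted as lost, while the endpoint includes them at zero.

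The size of any shortfall is not fixed by the document. It depends on the true share of zeros, the number effectively analysed, whether treatment changes that share, and the baseline correlation. With the plan's inputs, unadjusted power for an overall 0.1 m/sec lies between about 75% and 86%. The planned covariate adjustment could close that gap wholly or partly.

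This should be fixed. It does not undermine the endpoint, the analysis set or the model, each of which is clearly specified.

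**What to change.** Keep the 0 m/sec rule and the target of 198. Rewrite the sample-size section as follows:
- Base the calculation on the score as analysed, with the assumed share of zeros and the resulting SD stated (about 0.231 with the present inputs).
- Define the 0.1 m/sec effect as a difference in overall means, zeros included.
- State an assumed baseline-to-discharge correlation for the ANCOVA, with its basis, and show power over a range of values.
- Inflate only for outcomes that will truly be missing, and say how deaths and acute transfers are counted within the 25%.
- Report the power that 198 then delivers, and bring the abstract's power statement into line.

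The cost is a rewritten paragraph and possibly a less favourable stated power. Nothing in the conduct of the trial changes.

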### Statistical analysis

The primary analysis will be conducted on an intention-to-treat basis using data from all randomized participants, although a ‘per protocol’ analysis of the primary outcome will also be reported. Primary outcome values missing due to participants’ death will be imputed as zero. An independent adjudication panel, blinded to group assignment, will review records for participants’ who were discharged to an acute facility as medically unwell. Based on the reasons for transfer, the adjudication panel will determine whether the participant was likely to be able to walk and complete a 6-meter walk test at the time of transfer. If the adjudication panel determines the person was unlikely to be able to walk, the missing value will be imputed as zero. If the adjudication panel determines the person was likely to be able to walk, the last measure will be carried forward. Following that, multiple imputation of other missing primary outcome values will be conducted subject to the satisfaction of relevant missingness assumptions. Baseline data will be examined to ensure that the intervention and control groups are comparable using descriptive statistics with 95% confidence intervals.

All outcomes and analyses have been prospectively categorized as primary, secondary, or tertiary. Differences in both primary and secondary endpoints between the two arms of the study will be tested independently at the 0.05 level of significance. No formal adjustments will be undertaken to constrain the overall type I error associated with the secondary analyses. Their purpose is to supplement evidence from the confirmatory primary analysis to help more fully characterize the treatment effect. Results from the secondary analyses will be interpreted in this context.

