### Assessments

Each assessment will be completed at three time points by an assessor blinded to group allocation. All assessors will be trained to ensure the assessments are standardized and will be FIM^TM^ credentialed.

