#### Baseline

The baseline assessment will be completed within 48 hours of admission. In addition to primary and secondary outcome measures collected at baseline, additional demographic and clinical data will be obtained. These data will include the participant’s age, sex, height and weight, acute LOS, mental state (measured by the Mini Mental State Examination [42]), frailty (measured using the modified Fried Frailty Index) [43,44], co-morbidities (age adjusted Charlson Comorbidity Score [45]), depression (Geriatric Depression Scale [46]), medications, self (or carer) reported falls in the last 12 months and social situation.

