#### Discharge

The second assessment will be completed within 48 hours of discharge. Self-selected gait speed (primary outcome) at this assessment will be the primary endpoint of the study. In addition to the primary and secondary outcome assessments, discharge destination and service referrals on discharge will also be collected. For participants discharged to residential care, the day the treating team determined that they required residential care placement and required paperwork was completed will be used in lieu of actual discharge date for this analysis.

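### Carrying the last measure forward for acute transfers judged able to walk means carrying baseline forward: it assumes no recovery and can assign 0 m/sec against the panel's own finding

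*Protocol article*

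**What the plan says.** The Statistical analysis section of the protocol article sets out an ordered handling of missing discharge gait speed.

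- Deaths are imputed as zero.
- For participants discharged to an acute facility as medically unwell, an independent panel blinded to group "will determine whether the participant was likely to be able to walk and complete a 6-meter walk test at the time of transfer".
- For a negative finding: "If the adjudication panel determines the person was unlikely to be able to walk, the missing value will be imputed as zero".
- For a positive finding: "If the adjudication panel determines the person was likely to be able to walk, the last measure will be carried forward".
- Only after these steps, "multiple imputation of other missing primary outcome values will be conducted subject to the satisfaction of relevant missingness assumptions".

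On the measurement schedule, the Assessments section states: "Each assessment will be completed at three time points by an assessor blinded to group allocation". The first is at admission: "The baseline assessment will be completed within 48 hours of admission". It covers gait speed, since the Baseline section refers to the primary and secondary outcome measures collected then. The next is at the end of the stay: "The second assessment will be completed within 48 hours of discharge". The third is 6 months later.

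Two further rules matter. Under Primary outcome, a participant who cannot complete the walk test scores 0 m/sec. Under Randomization, non-ambulant people (Levels 1 and 2) are enrolled and form a stratum.

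**The concern.** The term last measure suggests a recent in-hospital reading, but the schedule contains none. The rule is baseline carried forward, applied to people chosen because they could probably walk when they left.

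Two things follow. First, the imputed change from admission is exactly zero in either arm, so these participants contribute neither recovery nor treatment effect to a trial that tests whether extra activity during the stay (anticipated average 19 days) improves gait speed. Second, for someone who scored 0 at admission, the positive and negative panel findings lead to the same value, which is also the value given for death. The adjudication then has no effect on the analysis.

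The rule sits in the confirmatory analysis. Multiple imputation is reserved for the other missing values, so the carried-forward number enters the ANCOVA as if it had been observed.

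**Working it through.** **1. What the last measure can be.** The planned gait-speed assessments are admission, discharge and 6 months. The discharge value is the one missing, and the 6-month value comes later. Only admission remains. If a discharge test was done before the transfer, nothing is missing and the rule does not apply.

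**2. Value assigned by case (discharge value missing).**

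| Situation | Value assigned |
|---|---|
| Died | 0 |
| Transferred, judged unlikely to walk | 0 |
| Transferred, judged likely to walk, baseline above 0 | baseline value |
| Transferred, judged likely to walk, baseline 0 | 0 |

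The last row contradicts the finding that produced it. It needs no outside figure. It applies to anyone who could not complete the test at admission, which the non-ambulant stratum makes likely for some participants.

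**3. The plan's own figure.** From Sample size estimation: difference 0.1 m/sec, two-sided alpha 0.05, power 90%, and 0.18 m/sec read as a standard deviation. Then n per group = 2 × (1.960 + 1.282)² × 0.18² / 0.1² = 68.1, rounded up to 69, as stated. Power at 69 per group is 90.4%. The total of 198 reproduces as 69 × 1.25 × 1.14 = 98.3, rounded up to 99 per group.

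**4. Size of the effect.** Let f1 and f0 be the shares under the rule in the intervention and control arms, G the mean recovery from admission to discharge in the control arm, and δ the true effect. None of f1, f0 or G is in the protocol. If those under the rule would otherwise have had the same G and δ as everyone else, the expected difference is

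(1 − f1)(G + δ) − (1 − f0)G = (1 − f1)δ − (f1 − f0)G.

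*Equal shares, δ = 0.10.* The second term vanishes and the difference is 0.10 × (1 − f). Power is recomputed with the standard deviation held at 0.18.

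| f in both arms (assumed) | Expected difference, m/sec | Power, 69 per group | Power, 99 per group |
|---|---|---|---|
| 0% | 0.100 | 90.4% | 97.4% |
| 2% | 0.098 | 89.2% | 96.9% |
| 5% | 0.095 | 87.3% | 96.0% |
| 10% | 0.090 | 83.6% | 94.0% |

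*Unequal shares.* The bias from imbalance is (f1 − f0) × G. A 5-point imbalance with G = 0.2 gives 0.05 × 0.2 = 0.010 m/sec. With G from 0.05 to 0.30 it ranges from 0.0025 to 0.015.

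**5. Check by simulation.** ANCOVA on baseline, 99 per arm, 4,000 runs per setting, assumed G = 0.2 and 30% with baseline 0.

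| f intervention / control | Estimate when δ = 0.10 | Estimate when δ = 0 | Rejection when δ = 0 |
|---|---|---|---|
| 0% / 0% | 0.100 | 0.000 | 6.0% |
| 5% / 5% | 0.095 | 0.000 | 4.9% |
| 10% / 10% | 0.090 | 0.000 | 5.1% |
| 10% / 5% | 0.081 | −0.010 | 7.8% |
| 5% / 10% | 0.104 | +0.010 | 7.3% |

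The formula gives 0.09 − 0.01 = 0.080 and 0.095 + 0.01 = 0.105 for the last two rows, in agreement. Rejection of 7% to 8% should be read against 5% to 6% in the balanced settings, which includes simulation noise.

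**The case against.** The strongest defence is that the rule is prespecified, is applied by a blinded independent panel, and is cautious. Someone transferred as medically unwell may well not have improved, and with equal transfer rates the rule only shrinks the effect. That is fair for the balanced case. It fails when transfers differ by arm, because the bias then goes in either direction. The section on risk management and safety monitoring itself names a possible increase in adverse events with the intervention, although it also reports no between-group difference in the pilot. Unequal transfer is plausible but not shown.

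The sizes are also open to challenge. The rule reaches only transfers who lack a discharge test and are judged able to walk, and their stays were cut short. Both G and δ may be smaller for them, so the figures above are more likely upper bounds. This stands. The baseline-0 contradiction is likewise a narrow case of unknown frequency.

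It might be said that defining the last measure is a matter for the analysis plan. But the article states the rule, and its own schedule fixes what the rule does.

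A reader might infer three stronger points that the protocol does not support.

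- *Standard errors are understated because a single imputed value is treated as observed.* In simulation with f = 10% in both arms and G = 0.2, the model standard error and the empirical one were both 0.0218, above the 0.0211 with nothing missing, because carried-forward values lie off the regression line and add residual variance. Null rejection stayed near 5%.
- *Up to 25% of participants could be affected.* The 25% in Sample size estimation is overall dropout, not the share under this rule.
- *Making multiple imputation conditional on missingness assumptions is itself a defect.* The wording is conventional, and faulting it would undercut the remedy proposed here.

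**Conclusion.** The point holds. As written, the primary analysis sets discharge gait speed equal to admission gait speed for transferred participants judged able to walk, and so assigns 0 m/sec to those who scored 0 at admission, against the panel's finding. Both conclusions follow from the protocol's text alone.

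The numerical consequence rests on assumptions about the share affected, its balance between arms and the mean recovery. Over the ranges shown it is a loss of 2% to 10% of the target effect with equal shares, and a bias of about one tenth of the 0.1 m/sec target with a 5-point imbalance and 0.2 m/sec recovery. That is modest unless transfers are frequent or unbalanced. The rule should be changed because it is internally inconsistent and the correction is cheap. It does not by itself invalidate the trial.

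**What to change.** In the primary analysis, set discharge gait speed to missing for transferred participants whom the panel judges likely able to walk. Include them in the multiple imputation already planned, with arm, baseline gait speed, mobility stratum and site in the imputation model, and constrain their imputed values to be above 0 so that the panel's finding is respected. Leave the zero for deaths and for those judged unlikely to walk. Keep the present rule, named plainly as baseline carried forward, as a sensitivity analysis.

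The cost is a change of analysis wording, with no new data collection and no change to the panel's work. The downside is a missing-at-random assumption for people who became unwell, which may be optimistic because their values would be modelled on participants who completed their stay. The baseline-carried-forward analysis addresses this by showing the result with no recovery assumed.
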